## Abstract

**Background:**

Late preterm and early term infants are a large proportion of all births. Historically, outcomes were thought to be similar to those of full term infants, but recent evidence demonstrates worse outcomes. Although serious morbidity is less common than in very preterm infants, the impact of modest illness in large numbers of more mature neonates is significant, with 30–40% requiring neonatal unit (NNU) admission, primarily for respiratory disease. The SurfON trial aims to evaluate whether early surfactant therapy improves outcomes compared with expectant management in late preterm and early term infants with respiratory distress. The primary objectives are to compare neonatal hospital stay and incidence of severe respiratory failure, with secondary objectives assessing other perinatal outcomes and cost-effectiveness.

**Methods:**

The SurfON trial is a multicentre, open-label, randomised controlled trial involving 45 UK NNUs, aiming to recruit 1522 infants over 30 months. Eligible infants are those born at 34^+0^ to 38^+6^ weeks’ gestation who require noninvasive respiratory support for respiratory distress within 24 h of birth. Infants are randomised in a 1:1 allocation ratio to either early surfactant therapy or expectant management. Infants randomised to the early surfactant therapy group will receive a single dose of CUROSURF^®^, a natural animal-derived surfactant. IMP administration reflects local site policy and procedure and may be completed by any clinician for whom this falls within their usual scope of practice, following confirmation of eligibility. The IMP is a commonly used drug in neonates and is being used in line with standard care. Side effects are uncommon and usually transient. Timing and dosage of IMP administration will be collected. Surfactant is a stock drug for all NNUs and will be administered and accounted for as per local practice.

**Discussion:**

Evidence-based guidance for the management of late preterm and early term infants is sparse, and no previous large randomised controlled trials have focused on this population. Management of respiratory distress in late preterm and early term infants varies. Some clinicians prefer early surfactant administration to prevent deterioration—78others delay treatment to avoid mechanical ventilation. This inconsistency highlights the need for trials to establish an evidence base. Unexpected neonatal morbidity and prolonged hospitalisation cause significant psychological distress for families, impacting breastfeeding and maternal well-being. High intensive care workload and associated costs pose challenges for the NHS (National Health Service). Evidence-based management could improve outcomes and reduce healthcare burdens.

**Trial registration:**

ISRCTN 15915394. Registered on 20th February 2020 https://www.isrctn.com/ISRCTN15915394.

## Administrative information

**Table Taba:** 

Title (1)	SurfON: multicentre, open-label, randomised controlled trial of early surfactant therapy versus expectant management in late preterm and early term infants with respiratory distress
Trial registration {2a and 2b}	ISRCTN: 15915394 — Registered 20th February 2020 https://www.isrctn.com/ISRCTN15915394
Protocol version {3}	SurfON Protocol Version 7.0 25th April 2025
Funding {4}	NIHR Health Technology Assessment (HTA) Programme

## Introduction

### Background and rationale {6a}

SurfON is a multicentre, open-label, randomised controlled trial of early surfactant therapy versus expectant management in late preterm and early term infants with respiratory distress. Around a third of all live births in England and Wales occur late preterm or early term (34^+0^–36^+6^ or 37^+0^–38^+6^ weeks of gestation, respectively). However, respiratory outcomes in this population remain a subject of ongoing debate and clinical uncertainty. While historically considered similar to full term infants, recent evidence suggests that these infants are at increased risk of both neonatal and long-term respiratory complications [1–9].

Respiratory disease is the most common reason for late preterm and early term infants to require neonatal unit (NNU) admission [10–12].

Respiratory distress syndrome (RDS) is a consequence of lung immaturity and deficiency of surfactant, a substance that reduces alveolar surface tension and improves lung compliance. The risk of RDS increases with decreasing gestation; however, although respiratory maturity is often assumed, it also occurs in late preterm and early term infants [13, 14]. Other common neonatal respiratory conditions cause secondary deficiency of surfactant production [14, 15]. While the benefits of early surfactant therapy have been established for very preterm infants (< 32-week gestation) [16, 17], its role in late preterm and early term infants with respiratory distress remains unclear. Current practice varies widely, with some clinicians opting for early intervention with the aim of preventing deterioration and others favouring a more expectant approach, with the aim of avoiding airway manipulation, potential complications, and costs associated with surfactant administration.

The lack of consensus about optimal management is partly due to the absence of high-quality evidence specific to this population. Existing studies have limitations in terms of sample size, study design, study population, and variability in clinical practices. This has resulted in a lack of clear guidance for clinicians, leading to inconsistencies in care.

The impact of respiratory illness in these infants extends beyond the neonatal period. Long-term respiratory morbidity, including impaired lung function and increased risk of respiratory infections, has been reported in individuals born both late preterm and early term [3, 5–8], and the underlying mechanisms and the role of early respiratory interventions in these long-term outcomes remain to be fully understood.

Given the significant clinical and economic burden associated with respiratory illness in late preterm and early term infants, there is a pressing need for evidence-based guidance on their management. A randomised controlled trial comparing early surfactant therapy to an expectant approach can provide valuable insights into the optimal timing and efficacy of this intervention. Such a trial would contribute to improving the care of these vulnerable infants and reducing the long-term consequences of respiratory disease.

### Objectives {7}

The trial will investigate whether, in late preterm and early term infants with respiratory distress, the early use of surfactant versus expectant management results in a shorter duration of hospital stay and fewer infants who fail to respond to treatment.

Primary objectives are as follows:

To compare duration of neonatal hospital stay in infants randomised to receive early surfactant versus those who received expectant management.To compare incidence of severe respiratory failure in infants randomised to receive early surfactant therapy versus those who received expectant management.

Secondary objectives are as follows:

To investigate the effects of early surfactant therapy versus expectant management on perinatal secondary outcomes.To investigate the cost-effectiveness of early surfactant therapy versus expectant management.

### Trial design {8}

This trial will be a pragmatic, multicentre, open-label, two-arm parallel-group, randomised controlled trial (RCT). An economic evaluation will be conducted alongside the clinical trial to assess the cost-effectiveness of early surfactant therapy versus expectant management.

A total of 1522 infants will be randomised to receive expectant management or early surfactant therapy. There will be a 12-month internal pilot phase, after which ‘stop-go’ criteria will be used to evaluate the feasibility of recruitment and other trial processes.

The trial data collection will be from trial entry until 1 year of age corrected for prematurity and will include screening, consent, treatment, and follow-up. Outcome information will be collected by case report forms (CRFs), with clinical data collection from medical records at the hospital. Questionnaires will be given to the mother at trial entry and around the time the infant is discharged from the hospital. Survival, paediatric secondary care use, and associated costs from discharge up to 1 year of age, corrected for prematurity, will be collected from a routine national database (e.g. HES), with no direct contact with the parent(s).

## Methods: participants, interventions and outcomes

### Study setting {9}

#### Study settings

The trial will be conducted across 45 neonatal units (NNUs) in the UK. Participating centres will include neonatal intensive care units (NICUs), local neonatal units (LNUs), and special care units (SCUs). For a full list of recruiting sites, please see Table 1: List of recruiting sites.

**Table 1 Tab1:** List of recruiting sites

NHS trust	Recruiting site (hospital)
Bedfordshire Hospitals NHS Foundation Trust	Luton & Dunstable University Hospital
Belfast Health and Social Care Trust	Royal Jubilee Maternity Hospital, Belfast
Betsi Cadwaladr University Health Board	Glan Clwyd District General Hospital
Betsi Cadwaladr University Health Board	Wrexham Maelor Hospital
Betsi Cadwaladr University Health Board	Ysbyty Gwynedd District General Hospital, Bangor
Birmingham Women’s and Children’s NHS Foundation Trust	Birmingham Women’s Hospital
Bolton NHS Foundation Trust	Royal Bolton Hospital
Countess of Chester NHS Foundation Trust	Countess of Chester Hospital
Dartford and Gravesham NHS Trust	Darent Valley Hospital, Dartford
East Kent Hospitals University NHS Foundation Trust	William Harvey Hospital, Ashford
East Suffolk and North Essex NHS FT	Ipswich Hospital
Epsom and St Helier University Hospitals NHS Trust	St Helier Hospital, Carshalton
Great Western Hospitals NHS Foundation Trust	Great Western Hospital, Swindon
Hull University Teaching Hospitals NHS Trust	Hull Royal Infirmary
Imperial College Healthcare NHS Trust	Queen Charlotte's & Chelsea Hospital
Imperial College Healthcare NHS Trust	St Mary's Hospital, London
Isle of Wight NHS Trust	St Mary's Hospital, Isle of Wight
King's College Hospital, London	King's College Hospital, London
Lancashire Teaching Hospitals NHS Foundation Trust	Royal Preston Hospital
Leeds Teaching Hospitals NHS Trust	Leeds General Infirmary
Liverpool Women's NHS Foundation Trust	Liverpool Women's Hospital
Maidstone and Tunbridge Wells NHS Trust	Tunbridge Wells Hospital
Manchester University NHS Foundation Trust	Saint Mary's Hospital, Manchester
Manchester University NHS Foundation Trust	Wythenshawe Hospital, Manchester
Medway NHS Foundation Trust	Medway Maritime Hospital
Newcastle upon Tyne Hospitals NHS Foundation Trust	Royal Victoria Infirmary, Newcastle
NHS Lothian	Royal Infirmary of Edinburgh
NHS Tayside	Ninewells Hospital and Medical School, Dundee
Norfolk and Norwich University Hospitals NHS Trust	Norfolk and Norwich University Hospital

### Eligibility criteria {10}

#### Inclusion criteria

Born at 34^+0^ to 38^+6^ weeks of gestation ≤ 24 h oldRespiratory distress defined as follows:*FiO*_*2*_ ≥ 0.3 and < 0.45 needed to maintain *SaO*_*2*_ ≥ 92%*FiO*_*2*_ < 0.3 with clinically significant work of breathingClinical decision to provide noninvasive respiratory supportWritten parental informed consent

#### Exclusion criteria

Major structural or chromosomal abnormalityNo realistic prospect of survivalPrior intubation and/or surfactant administrationKnown or suspected hypoxic ischaemic encephalopathyCongenital abnormality of the upper or lower respiratory tractKnown or suspected neuromuscular disorder

## Participants

The trial population is late preterm infants (born at 34^+0^ to 36^+6^ weeks of gestation) and early term infants (born at 37^+0^ to 38^+6^ weeks of gestation) with respiratory distress, where a clinical decision has been made to provide noninvasive respiratory support.

## Site selection and training

Sites are identified through a site selection feasibility process and agreed to by the PMG. At the time of randomisation, a delegated clinician or advanced/associate neonatal nurse practitioner (ANNP), as per local scope of practice and the site delegation log, confirms participant eligibility and completes randomisation. The intervention, surfactant, is a stock drug for all recruiting sites and is administered and accounted for according to local policy and practice.

Selection criteria include the mandatory requirement for PIs to be suitably qualified, possessing current *Good Clinical Practice (GCP)* certification and appropriate research experience. Sites must demonstrate and *confirm adequate capacity and capability* (e.g. facilities, specialist equipment, and sufficient staff and patient throughput) to conduct the study successfully. Furthermore, sites are strategically selected based on their potential to maximize the *generalisability* of study results, which is achieved by ensuring inclusive recruitment across diverse populations, including those from areas of high deprivation or ethnic minority groups.

### Who will take informed consent? {26a}

Clinicians, advanced neonatal nurse practitioners, and nurses can obtain consent. They must have GCP, SurfON study training, and be delegated to take consent by the PI.

### Additional consent provisions for collection and use of participant data and biological specimens {26b}

Not applicable as study design does not involve the collection of biological specimens from participants. There is no plan to use the participant data for future, unspecified research. Long-term consent was obtained to contact participants in the future about further related research.

## Interventions

### Explanation for the choice of comparators {6b}

#### Rationale for expectant management group

Infants in the expectant management group will, where possible, be maintained on noninvasive respiratory support alone, at least until a more severe disease threshold is reached, defined as follows:

Sustained (≥ 30 min) requirement for *FiO*_*2*_ ≥ 0.45 to maintain oxygen saturations (SaO_2_) ≥ 92%

The expectant management group serves as a control group to assess the natural course of respiratory disease in infants receiving only standard noninvasive respiratory support. This allows for the evaluation of the effectiveness of early surfactant therapy.

#### Rationale for early surfactant therapy group

Infants in the early surfactant therapy group will receive a single dose of surfactant administered as soon as possible after the infant has been randomised.

The early surfactant therapy group is designed to assess the potential benefits of early surfactant administration in improving outcomes for babies, mothers, and the NHS. This approach is based on the hypothesis that early intervention can prevent or limit deterioration in the respiratory condition and minimise the need for invasive respiratory support and mechanical ventilation, thus reducing the length of hospital stay for the baby and mother and associated costs.

#### Additional respiratory interventions

Information regarding the reasons for additional respiratory interventions and surfactant administration will be documented.

It is important to note that the decision to administer surfactant outside of surfactant administered according to allocation in either group will be based on the individual infant’s clinical condition and the attending clinician’s assessment of the risk-benefit ratio.

### Intervention description {11a}

The investigational medicinal product (IMP) is CUROSURF^®^, a natural animal-derived surfactant manufactured and supplied by Chiesi Farmaceutici S.p.A. at [name]. The Reference Safety Information (RSI) will be the latest approved Summary of Product Characteristics (SmPC) for the surfactant used.

The recommended starting dose for the IMP is 100–200 mg/kg (1.25–2.5 ml/kg), administered in a single dose as soon as possible after diagnosing respiratory distress. The administration of the IMP will be as per local site policy and procedure and may be completed by any clinician for whom this falls within their usual scope of practice, following confirmation of eligibility by a doctor or advanced neonatal nurse practitioner. As part of the intervention in this trial, surfactant will be given to infants as soon as possible after randomisation.

The IMP is a commonly used drug in NNUs and is being used in line with standard care. Side effects are uncommon and usually transient during administration.

The timing and dosage of IMP administration will be collected. Surfactant is a stock drug for all NNUs and will be administered and accounted for as per local practice. No specific contraindications are known.

### Criteria for discontinuing or modifying allocated interventions {11b}

Infants in the expectant management group should, where possible, be maintained on noninvasive respiratory support alone, at least until a more severe disease threshold is reached, defined as follows:

Sustained (≥ 30 min) requirement for *FiO*_*2*_ ≥ 0.45 to maintain oxygen saturations (SaO_2_) ≥ 92%.

In either study group, surfactant may be given if intubation is required for another reason or if the attending clinician deems this necessary. Information on the reasons for additional respiratory intervention and surfactant administration will be collected.

### Strategies to improve adherence to interventions {11c}

Non-adherence to the trial intervention, particularly within the early surfactant therapy group, is closely monitored throughout the trial. The Data Monitoring Committee (DMC) has established specific criteria for monitoring non-adherence, defining it as instances where infants in the early surfactant arm do not receive the trial intervention, documented solely as ‘clinician decision’ without further explanation, and occurring more than once at a site.

The Trial Management Team will proactively review site data for these instances. Sites meeting the DMC’s criteria will be contacted by the trial management team to investigate the reasons for non-adherence and implement targeted interventions to reinforce protocol compliance. The DMC also closely monitors non-adherence cases as part of its ongoing safety and efficacy oversight, ensuring appropriate action is taken to maintain trial integrity. Furthermore, clear documentation requirements are emphasised to discourage ambiguous ‘clinician decision’ justifications, promoting transparency and accountability.

### Relevant concomitant care permitted or prohibited during the trial {11d}

There are no contraindicated medications or dietary supplements, and infants will be able to have all medicines and supplements normally prescribed for this population during the trial.

### Provisions for post-trial care {30}

Infants who develop health problems unrelated to the trial intervention will continue to receive all necessary clinical care through the NHS as part of routine practice. The trial does not restrict or limit access to ancillary care for conditions arising during the neonatal period.

The investigational product, CUROSURF^®^ (surfactant), is a licensed drug routinely used within the NHS for neonatal respiratory distress. Surfactant is administered only during the acute phase of illness and is not required once infants are discharged from hospital. Therefore, there are no specific posttrial care arrangements, and participants will continue to receive all clinically indicated treatments through the NHS.

In the event of harm to a participant due to someone’s negligence during the research, participants have grounds for legal action for compensation against the sponsor. The National Health Service complaint mechanisms will also be available to participants.

### Outcomes {12}

The primary and secondary outcome measures are detailed in Table 2.

**Table 2 Tab2:** Primary and secondary outcome measures

**Outcome measures**	**Time point(s) of evaluation of this outcome measure**
•*Length of infant’s hospital stay* after birth, defined as the number of days from birth to discharge home from hospital	Between birth and discharge home from hospital
•*Incidence of severe respiratory failure*, defined as sustained (≥ 30 min) requirement for *FiO*_*2*_ ≥ 0.45 to maintain oxygen saturations (SaO_2_) ≥ 92%	Between trial entry and discharge home from hospital
**Perinatal clinical outcome measures**	**Time point(s) of evaluation of this outcome measure**
•*Total duration of NNU stay*, defined as total number of days of inpatient care in a neonatal unit (defined according to Healthcare Resource Group (HRG) Critical Care categories 1–5, 2016)	Between trial entry and infant discharge home from hospital
•*Total duration of neonatal intensive care*, defined as number of days of neonatal intensive care (defined according to HRG Critical Care categories 1–5, 2016)	
•*Duration of mechanical ventilation*, defined as days of ventilation via an ETT (endotracheal tube)	
•*Duration of noninvasive respiratory support*, using positive airway pressure or high flow	
•*Pulmonary air leaks*, requiring insertion of a chest drain	
•*Days of mother-infant separation*, defined using HRG Critical Care categories 1–5, 2016	
•*Breast milk feeding*, defined as (a) any breast milk feeding during neonatal hospital stay, (b) any breast milk feeding at hospital discharge, and (c) exclusive breast milk feeding at hospital discharge	
•*Late onset sepsis*, defined as the incidence of *microbiologically confirmed or clinically suspected* invasive infection more than 72 h after birth	
•*Need for inhaled nitric oxide (iNO) therapy*	
•*Need for extracorporeal membrane oxygenation (ECMO)*	
•*Medical respiratory diagnoses*, defined as any respiratory diagnosis attributed to the infant	
•*Surfactant administration*, defined as (a) administration of any additional surfactant in infants randomised to receive early surfactant or (b) administration of any surfactant in infants receiving expectant management, including number of doses and dose given	
•*Maternal length of hospitalisation*, defined as the total number of days spent by the mother in hospital after trial entry	Between trial entry and maternal discharge home from hospital
**Health economic outcome measures**	**Time point(s) of evaluation of this outcome measure**
•*Cost of maternal hospitalisation*	Between trial entry and infant discharge home from hospital
•*Self-reported maternal health-related quality of life*	
•*Costs associated with neonatal care*	
•*Survival, paediatric secondary care use, and associated costs* using routine national databases	Between infant discharge home and 1 year of age, corrected for prematurity

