## Assignment of interventions: blinding

### Who will be blinded {17a}

As SurfON is an open-label trial, participants and treating clinicians will not be blinded to treatment allocation. A validating statistician, who will remain blinded to treatment allocation, will independently check and confirm the primary comparative analyses after database lock. Full blinding of the trial statisticians is not possible, as interim reporting to the Data Monitoring Committee (DMC) requires an unblinded statistician to prepare safety and feasibility summaries. To limit potential bias, interim reports will be restricted to descriptive summaries only, without inferential comparisons between trial arms.

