## Data collection and management

### Plans for assessment and collection of outcomes {18a}

Prior to any data collection, the mother must provide informed consent. Once consent is obtained, the randomisation process is initiated by filling out the appropriate forms on the SurfON randomisation website where the infant will be allocated *to early surfactant therapy* or *expectant management*.

Data for the SurfON study will be collected primarily on electronic case report forms (eCRFs) within the OpenClinica clinical database. Mandatory CRFs include the consent form (paper), randomisation, contact details, trial entry, trial intervention, respiratory support log, outcomes, and mother’s entry and discharge questionnaire (if consent is provided). Additional CRFs may be required for certain participants, such as the surfactant, hospital transfer, withdrawal, SurfON serious adverse event, and SurfON incident and deviation forms. These forms will be completed as needed.

Outcome data will be collected primarily from existing hospital records and electronic data collection systems. Data will be entered on trial-specific CRFs by site staff, with the outcome CRF completed at hospital discharge. Optional questionnaires may be administered to mothers who have consented, assessing quality of life and breast milk feeding. Maternal quality of life will be assessed using the preference-based EQ-5D-5L instrument. If an infant is transferred to another hospital, the recruiting site will remain responsible for data collection.

Secondary care use and survival data will be obtained from available electronic national databases in the UK. Databases will include information on hospital inpatient admissions, outpatient visits, paediatric critical care, and mortality data. This will include Hospital Episode Statistics (HES) in England and the electronic Data Research and Innovation Service (eDRIS) in Scotland. Parental consent will be obtained at trial entry to allow for follow-up using routine national databases.

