### Plans to promote participant retention and complete follow-up {18b}

The Trial Co-ordinating Centre will maintain regular contact with all sites to ensure accuracy and completeness of all study documentation during the infants’ participation in the study. For infants who discontinue participation or where there is a deviation from protocol after the point of randomisation, sites will be asked to record reasons for this and to continue data collection for analysis of outcomes according to intention to treat.

Source data verification (SDV) is performed on the first 10 completed respiratory logs from each site, which record the primary outcome for the trial. Data are entered directly into OpenClinica, and paper copies are provided to the trial team for SDV checks. The trial team conducts manual SDV checks, provides individual feedback to sites, flags errors, and sends detailed emails highlighting common mistakes to prevent future errors. Additionally, the trial team hosts webinars, refresher training sessions, and drop-in sessions to address concerns and clarify proper completion of respiratory logs.

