For the severe respiratory failure primary outcome, risk ratios with 95% CI will be calculated using log-binomial regression or Poisson regression with a robust variance estimator in the event of non-convergence. Absolute risk difference and associated confidence intervals will also be calculated. 95% confidence intervals will be used for all comparative analyses, including subgroup analyses. *p*-values will be presented for the primary outcome comparisons with a two-sided 5% level of significance used for statistical inference. There will be no adjustment made for multiplicity when testing the two primary outcomes. Careful interpretation of the results will be based on the following: If both primary outcomes show evidence of superiority (i.e. evidence to reject the null hypotheses for both primary outcomes), this will be interpreted as providing robust evidence that early surfactant therapy is superior to expectant management. Similarly, if results show no evidence of a difference for both primary outcomes, this will be interpreted as providing no evidence that early surfactant therapy is superior to expectant management. In all other scenarios, the results will be interpreted cautiously and in the context of corroborating evidence from the secondary outcomes.

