#### Secondary outcomes

For binary outcomes, risk ratios and 95% CIs will be estimated, following the same planned analysis as for the severe respiratory failure outcome. For normally distributed continuous outcomes, mean or median differences with 95% CIs will be calculated using linear regression. If the data show significant skewness, median differences with 95% CIs will be calculated using quantile regression. As per the primary outcomes, both crude and adjusted estimates will be presented, but the primary inference will be based on estimates adjusted for minimisation factors.

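### Late onset sepsis counts confirmed and merely suspected infection as one event in an open-label trial, so an arm difference could reflect suspicion rather than infection

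*Protocol article*

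**What the plan says.** Outcomes {12}, Table 2, lists late onset sepsis as a single incidence of "microbiologically confirmed or clinically suspected" "invasive infection more than 72 h after birth". An infant with positive microbiology and an infant in whom infection was only suspected are the same event.

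On blinding, Who will be blinded {17a} states that "participants and treating clinicians will not be blinded to treatment allocation". The one blinded role named there is a validating statistician for the primary comparisons.

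On data capture, Plans for assessment and collection of outcomes {18a} says "Outcome data will be collected primarily from existing hospital records and electronic data collection systems" and "Data will be entered on trial-specific CRFs by site staff". Plans to promote participant retention and complete follow-up {18b} adds that "Source data verification (SDV) is performed on the first 10 completed respiratory logs from each site". Sepsis is not mentioned there.

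On analysis, the Secondary outcomes section says "For binary outcomes, risk ratios and 95% CIs will be estimated". The Primary outcomes section says that when the two primaries neither both show superiority nor both show no difference, results are read cautiously and "in the context of corroborating evidence from the secondary outcomes". It excludes no secondary outcome from that role.

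**The concern.** The definition adds a laboratory finding to a judgement. The judgement is made by staff who know the allocation, and the article describes nothing for this outcome that would limit or reveal a difference in judgement between arms. No blinded assessor or adjudication is stated, the source data verification described covers respiratory logs, and the article says that no sensitivity analyses are planned.

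If suspected-only cases outnumber confirmed ones, the pooled risk ratio mainly follows the suspected part. A reader given only the pooled figure could not tell fewer infections from fewer suspicions. At stake is the reading of this one secondary outcome, and its use as supporting evidence when the primary results are mixed.

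**Working it through.** **1. The text.** Table 2 already separates outcomes whose parts mean different things: breast milk feeding has parts (a), (b) and (c), and surfactant administration has (a) and (b). It ties pulmonary air leak to a concrete act, insertion of a chest drain. Sepsis has neither a split nor an anchoring act for its suspected part.

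**2. Number per arm.** The article gives no sepsis rate, effect or power, so there is no sepsis figure to reproduce. The number per arm comes from Sample size {14}. Its recruitment target reproduces: 1280 × 1.13 / 0.95 = 1522.5, against 1522 stated. From this:
- after 5% attrition: 1522 × 0.95 / 2 = 723 per arm;
- also removing the 1.13 factor for multiple births: 1522 × 0.95 / 1.13 / 2 = 640 effective per arm.

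**3. Assumed inputs (none from the documents).** Confirmed infection c = 0.5% or 1%, the same in both arms. Suspected-only infection s = 3% to 10% in the reference arm, and 25% lower in the other arm purely through labelling.

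**4. Pooled risk ratio.** RR = (c + 0.75s) / (c + s).
- c = 0.5%, s = 10%: 8.0 / 10.5 = 0.76
- c = 1%, s = 3%: 3.25 / 4.0 = 0.81

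The risk ratio for confirmed infection is 1 in every scenario, by construction.

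**5. Chance that the 95% interval excludes no difference.** With p1 and p2 the pooled rates, p̄ their mean and n per arm, use Φ[(|p1 − p2| − 1.96·SE0) / SE1], where SE0 = √(2p̄(1 − p̄)/n) and SE1 = √((p1(1 − p1) + p2(1 − p2))/n). This is a normal approximation on the risk-difference scale, taken as a guide to the risk-ratio interval.

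Example with c = 1%, s = 3%, n = 723: p1 = 0.0400, p2 = 0.0325, SE0 = 0.00983, SE1 = 0.00983. Then (0.0075 − 0.01927) / 0.00983 = −1.20, and Φ = 11.6%.

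| c | s | p1 v p2 | RR | n = 723 | n = 640 |
|---|---|---|---|---|---|
| 1% | 3% | 4.0% v 3.25% | 0.81 | 12% | 11% |
| 0.5% | 3% | 3.5% v 2.75% | 0.79 | 13% | 12% |
| 1% | 10% | 11.0% v 8.5% | 0.77 | 36% | 33% |
| 0.5% | 10% | 10.5% v 8.0% | 0.76 | 37% | 34% |

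The nominal rate is 5% over both directions. The choice between 723 and 640 makes little difference.

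**6. What the confirmed component can show.** At c = 0.5–1% the expected count is about 640 × 0.005 = 3 to 723 × 0.01 = 7 infants per arm. By the same formula, a true halving of confirmed infection would be detected with about 11–20% power.

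**The case against.** The strongest reply is that the article condenses a fuller protocol and defers detailed methods to an SAP that is not shown. Criteria for suspected infection and a table by component may well be there. That stands, and it rules out saying that the trial will never report confirmed infection separately. It does not remove the point, because Table 2 itself fixes the outcome as pooled.

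A reader might infer that a biased sepsis result could tip the trial's conclusion. The documents do not support that. Sepsis is one of 13 perinatal secondary outcomes, the corroboration clause has no decision rule, and secondary outcomes have no stated role when the primaries agree. The article mentions p-values only for the primary comparisons. The most that would be visible is a confidence interval excluding 1.

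The illustration can also be called circular: it assumes a difference in suspicion and then finds it. That is fair. No passage gives the size or direction of such a difference, so the figures show sensitivity, not likelihood.

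It might be added that respiratory deterioration prompts suspicion of infection. That would happen in a blinded trial too and could be a genuine downstream effect of treatment, so the point does not rest on it.

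Other outcomes in Table 2, such as the respiratory diagnosis attributed to the infant, also involve discretion in an open-label trial. True, but sepsis has a laboratory-based component that can be shown separately at little cost.

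**Conclusion.** The point holds as one about the stated definition. Confirmed and suspected infection are a single event, suspicion is formed by unblinded clinicians, no blinded assessment is stated, and the outcome is among those that may be cited as corroboration for mixed primary results. A difference in the pooled outcome could therefore reflect differential suspicion.

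Its size cannot be derived from the documents. Under the assumed rates and an assumed 25% difference in suspicion, the pooled risk ratio is about 0.76–0.81 and the interval excludes 1 in about 11–37% of trials with no true effect. The primary tests and the sample size are untouched.

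It would go too far to demand that the confirmed component alone count as corroboration and that the pooled outcome become merely descriptive. With 11–20% power for a true halving at the assumed rates, confirmed infection cannot carry that role alone. It is also less exposed to unblinded judgement rather than immune: as an inference of this review, a sample has to be taken before infection can be confirmed.

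**What to change.** In Table 2, list late onset sepsis in two parts, as the table already does for breast milk feeding: (a) microbiologically confirmed; (b) confirmed or clinically suspected. Analyse both by the binary method already stated for secondary outcomes. In the interpretation text, add that when sepsis is cited as corroboration, the report states whether (a) is consistent with (b) and does not rely on (b) alone.

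Sample size, randomisation and treatment do not change. The cost is wording and one more table row, provided the CRF already records the two components separately. The article does not say whether it does. If not, the components would have to be retrieved from hospital records, and Trial status gives 30 April 2025 as the end of recruitment. The interval for (a) will be wide and should be presented as such, not read as evidence of no difference.
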